### Randomization

Patients will be centrally randomized by PCRUB-BBRI in a 1:1 ratio into the two study groups. A researcher who is independent of the organization responsible for managing the study will randomly allocate patients to groups using a computer-based random number generator.

### Evaluation

Evaluation of the Bizi Orain exercise program involves measuring the uptake, safety, adherence, and effectiveness of the program. These analyses incorporate elements of the reach, effectiveness, adoption, implementation, and maintenance (RE-AIM) framework [25]. Evaluation of the effectiveness of the program involves comparisons among the preprogram, postprogram, and follow-up assessments. The evaluation will be undertaken yearly from the beginning of the recruitment (2019) and will proceed until the target sample size is achieved.

#### Uptake

The proportion of people participating in the Bizi Orain exercise program out of all people with cancer in the province of Bizkaia (Basque Country) who are eligible will be reported as the participation rate. People with cancer who register for the program but do not commence their participation will also be reported. The representativeness of the participants will be determined by comparing their demographic and clinical characteristics to those of the people diagnosed with cancer in Bizkaia. Information about cancer diagnoses will be derived from the Basque Health System Registry (Osabide).

#### Safety

The incidence and severity of any adverse events (ie, falls, muscle strains) that occur during the health center–based sessions will be monitored and reported by the supervising exercise physiologist/nurse using program-specific documentation. Additionally, participants will be asked to self-report the incidence and severity of any adverse events they experience during health center–based sessions or home-based exercise using program-specific documentation.

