**Conclusions:**

Bizi Orain is the first population-based exercise program in Spain that will offer more insight into the implementation of feasible, generalizable, and sustainable supportive care services involving structured exercise to extend survival of patients with cancer, improve their physical function and quality of life, and reverse the adverse effects of their disease and related treatments, thereby reducing the clinical burden.

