Despite the established benefits of exercise for patients with cancer and calls to include it as an integral part of cancer treatment, the chances of this information reaching patients are considerably reduced by the self-reported lack of knowledge among oncologists concerning how to properly promote and prescribe exercise [14,15] and paucity of translation strategies for integrating efficacious exercise programs into routine cancer care [16]. Unfortunately, only ~13% of patients with cancer meet international PA guidelines objectively measured with accelerometers [17].

Nonetheless, in recent years, community-based oncological exercise programs have been gaining prominence. LIVESTRONG at the Young Men’s Christian Association (YMCA) [18,19] is a community-based exercise program that has shown sustainable benefits in terms of physical function and self-perceived health. Our previous findings from the “Eficancer” study also indicate that exercising thrice a week during a 12-week individually tailored exercise program conducted at local health centers can improve quality of life and physical function, and these improvements are sustained over time [20].

Exercise program accessibility remains a challenge in implementing the international PA guidelines, but this challenge could be mitigated with strategies and pathways that connect patients with exercise-related resources and a well-designed behavioral intervention program to counteract the common barriers to exercise faced by patients with cancer during and after first-line treatments [21]. Further, the long-term effects on the PA levels, physical function, survival, and cost-effectiveness of large-scale community-based programs that are accessible and generalizable to a large proportion of patients with cancer (ie, administered in a standard supportive care setting) are unknown.

The main objectives of this study are as follows:

to examine the effects attributable to an exercise program on physical function, and quality of life, and adverse effects compared to health habit prescriptions, and to explore whether these effects vary by cancer type, stage and treatments, age, or sexto analyze the association between the actual exercise dose (ie, number of sessions and exercise intensity, objectively measured PA level with accelerometers) and measured outcomesto assess the cost-effectiveness of the program

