#### Health Economics

An economic evaluation will be performed in parallel with the trial to assess the health benefits, additional costs, and potential savings of including exercise therapy as a standard of care for patients with cancer. This health economics analysis will provide the relative value for money of exercise medicine compared with other health care interventions in this patient population, stratified by age, cancer type, point along the cancer continuum, and stage of the disease. Hospital resource usage and associated costs will also be assessed to compare the costs of secondary health care utilization between the intervention and reference (usual care+PVS) groups. All hospital events, including emergency department attendances and admissions, outpatient visits and procedures, and inpatient admissions for all causes will be explored to quantify and identify potential disease-related events, as well as the total health care resource use for all other purposes inclusive of comorbidities and other chronic diseases. The cost of providing the supervised exercise and PVS interventions will also be quantified. Health benefits will be measured in terms of the quality of life based on the SF-6D utility index derived from the SF-36 and converted to a health utility score to obtain quality-adjusted life years for cost-utility analysis [40].

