#### Adverse Events

An external committee will review and compare all nonserious adverse events, whereas researchers will be obliged to report any serious adverse events to the research unit by email. A coordination committee with access to all the information it needs will undertake preliminary analyses of the data to monitor the safety of the program. This committee will be composed of individuals who are independent of the organization responsible for managing the study and members of the research team including the study coordinator; all are blind to patient allocation. In addition to serving on the committee, the coordinator will telephone the participating health centers daily to check on the progress of the study, report weekly on this progress to the principal investigator of the study, produce a monthly report with the study data, and provide recommendations to the study management team.

The trial was registered on January 18, 2019 (Clinical Trials.gov NCT03819595).The protocol has been approved by the local Clinical Research Ethics Committee (CEIC de Euskadi, PI2019016).

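### Nonserious adverse events are recorded only around exercise, so comparing them with the PVS arm rests on unequal ascertainment

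*Protocol article*

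**What the plan says.** The Safety section gives two routes for recording adverse events. Supervising staff record events at the health centers: "The incidence and severity of any adverse events (ie, falls, muscle strains) that occur during the health center–based sessions will be monitored". In addition, "participants will be asked to self-report the incidence and severity of any adverse events they experience during health center–based sessions or home-based exercise". Both routes use the program's own forms.

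Program Design allocates patients 1:1 to exercise plus the PVS counseling or to PVS alone. The PVS group starts the exercise program only after the assessments that close the 3-month randomized phase.

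The Adverse Events section stands under the secondary effectiveness outcomes and says: "An external committee will review and compare all nonserious adverse events, whereas researchers will be obliged to report any serious adverse events". The serious-event reports go to the research unit.

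Two other places bear on the point. The first main objective in the Introduction concerns effects "on physical function, and quality of life, and adverse effects compared to health habit prescriptions". Health Economics compares secondary health care use between the arms and states: "All hospital events, including emergency department attendances and admissions, outpatient visits and procedures, and inpatient admissions for all causes will be explored".

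**The concern.** A comparison of adverse events between arms needs the same events to be looked for in the same way and over the same period in both. Here the recording rule follows exposure to the intervention. The exercise arm has a supervisor, a form and scheduled sessions at which events are noted. The PVS arm has none of these during the randomized phase. A fall at home or a strain on an ordinary day lies outside the stated rule in either arm.

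Two things are at stake. Minor harms of exercise would look larger relative to PVS than they are, because the comparison group is hardly observed. And a plausible benefit of better strength and balance, namely fewer falls and injuries in daily life, would go unseen unless the event led to hospital contact.

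**Working it through.** The plan states no adverse-event rate, so there is no figure of its own to reproduce. The check sets recording time side by side and then works out what the recorded contrast measures.

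**Inputs**
- Two supervised sessions and one independent walking session a week for 12 weeks (Exercise Intervention).
- Supervised session of 1 to 1.25 h (Group Exercise Sessions).
- Walking session of 30 to 40 min (the walking paragraph that follows Table 1).
- PVS arm: no program sessions until after the 3-month assessments (Program Design).

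**Time under recording, exercise arm**
- Lower: 2 × 1 h + 0.5 h = 2.5 h a week; 2.5 / 168 = 1.5% of the week; 2.5 × 12 = 30 h in total.
- Upper: 2 × 1.25 h + 40/60 h = 3.17 h a week; 3.17 / 168 = 1.9%; 3.17 × 12 = 38 h in total.

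**Time under recording, PVS arm**
- Sessions: 0 h.
- Own exercise at home: possibly some, since PVS promotes physical activity and the self-report route speaks of participants in general. The article describes no form for it in this arm.

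**What the recorded contrast measures.** Take mean nonserious events per participant over the randomized phase. In the exercise arm, let E_in be events during exercise and E_out all others. In the PVS arm, let C_in be events during the patient's own exercise and C_out all others.
- Contrast wanted: (E_in + E_out) − (C_in + C_out).
- Contrast recorded, if PVS patients report every event in their own exercise: E_in − C_in.
- Recorded minus wanted: C_out − E_out.

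The error is therefore exactly the difference in events outside exercise, which is where a protective effect would show. If exercise lowers that count, the recorded contrast overstates net harm by the full amount of the benefit.

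**No true effect.** Suppose both arms have the same constant rate λ per hour and PVS patients record nothing. The wanted difference is 0. The recorded counts are 30λ to 38λ per exercise participant against 0 per PVS participant. Exercise shows an excess by construction, and a risk ratio has a denominator at or near zero.

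**Limit on the direction.** If exercise causes trouble noticed only after the session, E_out can exceed C_out, and the error in the difference then favors exercise. The stated direction assumes that exercise leaves unchanged, or lowers, the rate of minor events outside exercise time.

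**The case against.** Several points on the other side stand.

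- **Not all adverse events are tied to exercise.** The duty to report serious events covers any such event, without limit to sessions or to one arm.
- **A hospital contrast already exists.** Health Economics compares all-cause emergency, outpatient and inpatient use between arms. A reader might infer that a reduction in hospitalization could not be shown; that section says otherwise.
- **The objective may mean something else.** A reader might take "adverse effects compared to health habit prescriptions" as a promise to compare adverse events and conclude that no comparison with PVS is possible. The article also uses the term for consequences of the illness and its therapy, as in "reverse the adverse effects of their disease and related treatments". On that reading the fatigue, pain and nausea scales of the QLQ-C30, together with FACIT-Fatigue, serve the objective in both arms.
- **Oversight.** A reader might infer that serious events get no independent review, or that a committee of which "all are blind to patient allocation" is said cannot see an imbalance. Neither follows. Naming the research unit as recipient does not mean that reports stop there. The coordination committee has independent members and full access to information, and Quality Control mentions a data monitoring committee. Blinded members can review masked groups.
- **Recording by session has a purpose.** It is a sensible measure of the program's own safety.
- **The article is condensed.** Operational manuals and forms are mentioned but not shown.

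The last point does not remove the problem. The Safety section states a collection rule rather than leaving one open, and that rule does not supply what the Adverse Events section says will be compared. The one remaining escape is that the committee's comparison is not meant to be between arms. In a two-arm trial that is the less natural reading, and the text should then say so.

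**Conclusion.** The point holds for nonserious adverse events. As written, recording covers about 30 to 38 hours per exercise-arm participant over 12 weeks and no session time in the PVS arm, while all nonserious events are to be compared as a secondary outcome. Such a comparison between arms would be biased by unequal ascertainment. It would run against exercise for minor events, subject to the assumption on events outside exercise time, and it could not show a reduction in falls or injuries that do not lead to hospital contact.

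The conclusion rests on reading the committee's comparison as one between arms and on the Safety section being the full rule for nonserious events. Without an event rate, the bias cannot be put in events or as a ratio.

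The point does not extend to serious events or hospital use, which can be compared, and it leaves the primary outcomes untouched. It is a modest flaw that is cheap to repair.

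**What to change.** Reconcile the Safety and Adverse Events sections as follows.

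1. At the existing 3-month assessment, ask both arms the same adverse-event question, covering randomization to that visit and not limited to exercise. Use the answers for the between-arm comparison of nonserious events.
2. Use the all-cause hospital and emergency data already planned under Health Economics as the supporting contrast for serious events. Restrict it to the same window, because the PVS arm starts the program afterward.
3. Report session-related events separately, as a descriptive rate per session in the exercise arm, with no between-arm test.

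The cost is one added question per participant, which relies on recall over 3 months, and a small amendment. Patients already past the 3-month visit will not have been asked in this way. For them, rely on the hospital data and label session events as descriptive only.

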#### Adherence

Attendance at health-center–based exercise sessions and the reason for any missed sessions will be tracked throughout the program. Adherence to the recommended amounts of PA for cancer survivors [26] is to be assessed by 7-day accelerometer recordings obtained from a randomly selected subset of the participants. Further, completion of assessments at preprogram and postprogram time points as well as follow-up questionnaires will be reported. Compliance with the Bizi Orain exercise program procedures by exercise physiologists/nurseries at each site will be monitored through evaluation of program documentation (ie, screening, assessment, and exercise prescription documents).

### Effectiveness: Primary Study Outcomes

#### Physical Function (Clinical)

Physical function is assessed by 400-m walk tests in a 20-m corridor, repeated chair stand tests (5 times), and handgrip dynamometry tests [27-29]. Each participant will perform a graded submaximal cardiopulmonary exercise test (CPET) on an electric braking cycle-ergometer (ergoline GmbH, ergoselect 4) in the laboratory of the University of Deusto in a controlled environment (temperature, ±21 ºC; relative humidity, 50%-55%; barometric pressure, ±720 mm Hg). Briefly, the test protocol involves an unloaded 5-min warm-up followed by 1-min stages with 10-W workload increments from an initial workload of 20 W [30]. Participants will be asked to maintain a steady cadence between 60 to 70 rpm. Gas exchange will be recorded breath by breath using a CPET machine (Geratherm Ergostik). The test is performed until confirmation of at least one of the following criteria: (1) The second ventilatory threshold or the so-called “respiratory compensation point” (RCP) is observed from the Wasserman figures (respiratory equivalents, and O_2_ and CO_2_ partial pressure changes). (2) The respiration exchange ratio (RER)>=1.05 and rating of perceived effort (RPE)>8 on the 0-10–point Borg scale [31]. (3) Participants exhibit volitional exhaustion without meeting the previous criteria.

From a pragmatic viewpoint and owing to the difficulties of performing a CPET in a community-based program setting, the results obtained from the CPET will not be used for individualized prescriptions of exercise intensity during the sessions. However, these results (ventilatory threshold heart rates) will be used to evaluate the actual exercise intensity undertaken by participants when following a standard exercise prescription based on simpler cost-effective methods like RPE and estimated heart rate reserve (HRR).

The maximal strength in the upper and lower body will be measured in terms of the 5-repetition maximum (5RM) (the maximum load that can be lifted five times) in chest and leg press exercises, respectively [32]. These assessments are to be conducted by an independent exercise physiologist not involved with administering the exercise intervention.

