**Methods:**

This will be a hybrid study. In the first experimental phase, patients diagnosed with any type of cancer will be randomized into two parallel groups. One group immediately performs Bizi Orain, a 3-month supervised exercise program (3 times a week), in addition to behavioral counseling in a primary health care setting; the other is a reference group that starts the exercise program 3 months later (delayed treatment). In the second observational phase, the entire cohort of participants will be followed-up for 5 years. Any person diagnosed with cancer in the previous 2 years is eligible for the program. The program evaluation involves the uptake, safety, adherence, and effectiveness assessed after completion of the program and with follow-ups at 3, 6, 12, 24, 36, 48, and 60 months. The primary outcomes of the experimental study, to be compared between groups, are improved physical function and quality of life, whereas overall survival is the main objective of the prospective study. To analyze the association between changes in physical activity levels and overall survival, longitudinal mixed-effects models will be used for repeated follow-up measures.

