#### Patient-Reported Outcomes (Clinical)

A series of questionnaires with sound psychometric properties are to be used to assess general health and cancer-specific quality of life and cancer-related fatigue. The Medical Outcomes Study 36-Item Short-Form Health Survey (SF-36) is used to assess general health-related quality of life status across physical functioning, physical role functioning, bodily pain, general health, vitality, social functioning, emotional role functioning, and mental health domains (higher scores indicating a greater quality of life) [33]. Cancer-specific quality of life is evaluated by the core quality of life (QLQ-C-30) questionnaire developed by the European Organization for Research and Treatment of Cancer (EORTC) [34]. This questionnaire includes five functional domains (physical, role, cognitive, emotional, and social, with higher scores representing greater function/quality of life) and three symptom scales (fatigue, pain, and nausea, with lower scores indicating greater quality of life/less symptom severity). The General Health Questionnaire (GHQ-12) is administered to assess the psychological morbidity and possible psychiatric disorders [35]. Cancer-related fatigue is assessed using the Functional Assessment of Chronic Illness Therapy-Fatigue (FACIT-Fatigue) scale [36]. Finally, the Spanish version of the Alcohol Use Disorders Identification Test (AUDIT) is administered to screen for harmful alcohol consumption [37].

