**Statistical Analysis**

Data will be analyzed on an intention-to-treat basis with the maximum likelihood imputation of missing values, comparing average change scores at 3 months of follow-up (postintervention) among participants randomly assigned to the Bizi Orain or PVS groups. These analyses will include standard descriptive statistics, Student *t* tests, and analysis of covariance models adjusted for baseline values. These models will be extended to include clinically relevant covariates. Subgroup analyses will be conducted by cancer site and treatment status. Investigations into responders and nonresponders will be conducted to explore the heterogeneity of the intervention effect. To analyze the association between changes in the PA over time and outcome variables, longitudinal mixed-effects models will be used for repeated measures throughout the 5 years of follow-ups. Cox proportional hazards models will be used for survival analysis. No imputation method will be used to handle missing data as longitudinal mixed-effect models based on maximum likelihood estimation are more appropriate to handle missing data [49] than common imputation methods such as the last observation carried forward, complete case analysis, or other possible forms of imputation.

Finally, the incremental cost-effectiveness, cost-utility ratios, and confidence intervals will be calculated through bootstrapping and sensitivity analyses. All the analyses will be performed with SAS (version 9.4, SAS Institute) and R (version 3.6, R Core Team) statistical packages.

We have a network of 6 exercise laboratories with a capacity to include at least 1013 patients during the 2 years of recruitment. Assuming a 30% rate of loss (including deaths) throughout the year of follow-up, the study has a power of 80% to detect a difference in functional capacity between comparison groups, of at least 9 s in the 400-m walk test at 3 months as significant (α=.05), assuming a standard deviation of 95 m. Regarding the quality of life, the study has a power of over 90% to detect differences of 5 points between groups as significant (α=.05).

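### Every function test and questionnaire is labelled primary, while the trial is sized on the 400-m walk and an unnamed quality-of-life score, each at α=.05 with no rule for success.

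*Protocol article*

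**What the plan says.** - **Abstract, Methods.** "The primary outcomes of the experimental study, to be compared between groups, are improved physical function and quality of life". These are two domains; no variable is named. The abstract's Objective speaks instead of cardiorespiratory functional capacity and quality of life.
- **Effectiveness: Primary Study Outcomes, Physical Function (Clinical).** Three tests come first: "Physical function is assessed by 400-m walk tests in a 20-m corridor, repeated chair stand tests (5 times), and handgrip dynamometry tests". The same section adds "Each participant will perform a graded submaximal cardiopulmonary exercise test (CPET") and the 5-repetition maximum "in chest and leg press exercises, respectively". No outcome variable is named for the exercise test. Its stated use is to judge the intensity at which participants actually trained.
- **Same heading, Patient-Reported Outcomes (Clinical).** The opening sentence reads: "A series of questionnaires with sound psychometric properties are to be used to assess general health and cancer-specific quality of life and cancer-related fatigue". The instruments are the SF-36 (eight domains), the QLQ-C30 (five functional domains and three symptom scales as described), GHQ-12, FACIT-Fatigue and AUDIT. AUDIT is there to screen for harmful drinking. Secondary outcomes begin only after this section and the one on overall survival.
- **Statistical Analysis.** Power is stated for 9 s in the 400-m walk at 3 months (80%, α=.05). For quality of life the article claims that "the study has a power of over 90% to detect differences of 5 points between groups as significant (α=.05"). Neither the scale nor its standard deviation is given. The between-group methods are t tests and baseline-adjusted analysis of covariance.
- **Evaluation.** The programme evaluation, which includes effectiveness, is yearly: "The evaluation will be undertaken yearly from the beginning of the recruitment (2019) and will proceed until the target sample size is achieved".

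**The concern.** Three parts of the article give three different answers to what is primary: two domains, some two dozen measures, or two scores of which one is unidentified. A reader cannot tell which comparison decides the trial, or whether one or both domains must succeed.

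Followed as written, a positive claim could rest on any measure under the primary heading. An ineffective programme would then have more than a 5% chance of being reported as effective. The quality-of-life score could also be settled on after the results are known, because nothing in the text fixes it.

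**Working it through.** **1. The plan's own power figures.** Inputs from Statistical Analysis: 1013 patients and 30% loss; 1:1 allocation from Randomization. Evaluable: 1013 × 0.7 = 709.1, or 354.5 per arm. Power = Φ(δ / (SD·√(2/n)) − z), with z = 1.960 at two-sided 0.05.

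- *Walk, 9 s, SD 95:* 9 / (95 × √(2/354.5)) = 1.261; Φ(1.261 − 1.960) = 24%. With all 1013 patients it is 33%. The stated 80% does not reproduce, and the SD is printed in metres against a difference in seconds. That is a separate problem; below, 80% is taken as the nominal figure.
- *Quality of life, 5 points:* no SD is given. Power above 90% requires SD ≤ 5 / (√(2/354.5) × (1.960 + 1.282)) = 20.5. At an assumed SD of 20 it is 91%; at 15, 99%; at 25, 76%.

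**2. Count of trial-phase measures under the primary heading.**

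| Group | Number |
|---|---|
| Walk, chair stand, handgrip, exercise test, two 5RM tests | 6 |
| SF-36 domains | 8 |
| QLQ-C30 scales as described | 8 |
| GHQ-12, FACIT-Fatigue, AUDIT | 3 |
| Total | 25 |

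Without the exercise test (no variable named) and AUDIT (a screen) it is 23. Overall survival is under the same heading but belongs to the observational phase, so it is not counted.

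**3. Chance of at least one false positive, each test at two-sided 0.05.** With independent tests it is 1 − 0.95^k. With equally correlated normal statistics it comes from simulation (200,000 draws). The correlations are assumptions.

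| What may count as success | Independent | ρ = 0.3 | ρ = 0.5 | ρ = 0.7 |
|---|---|---|---|---|
| Either powered comparison (k = 2) | 9.75% | 9.5% | 9.0% | 8.4% |
| Any listed measure (k = 25) | 72% | 61% | 47% | 32% |

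With k = 23 and independence it is 1 − 0.95^23 = 69%. If both powered comparisons had to succeed, the error would not exceed 5%. The article does not say that they must.

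**4. Power at 0.025 each (z = 2.241).**

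- *Walk, nominal 80%:* Φ(0.842 + 1.960 − 2.241) = Φ(0.560) = 71%. On the printed inputs, Φ(1.261 − 2.241) = 16%, against 24% at 0.05.
- *Quality of life, SD 20:* 5 / (20 × √(2/354.5)) = 3.329; Φ(3.329 − 2.241) = 86%, against 91% at 0.05. At SD 20.5, the largest that fits the plan's claim, it is Φ(1.282 + 1.960 − 2.241) = 84%.

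**The case against.** **No text says that 25 measures are each tested at 5%.** This stands. The level is written only for the walk and for quality of life, and the questionnaire domains are listed to describe the instruments. A reader might infer a 72% error rate. The document does not support that as the trial's error rate: it needs 25 confirmatory tests that are nowhere stated, and independence between scales completed by the same patients. It is an upper bound for an illustration.

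**The function endpoint can be identified.** Largely true. Statistical Analysis ties functional capacity to the 400-m walk at 3 months, so a free choice of function score after the fact is a weak charge. It does not help the quality-of-life score, and it does not remove the other tests from under the primary heading.

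**The yearly evaluation adds repeated looks.** A reader might infer an inflated error from this too. The Evaluation section describes comparisons among preprogram, postprogram and follow-up assessments. It mentions no between-arm test, threshold or stopping rule, so no inflation figure is claimed. Because effectiveness is part of that evaluation, a clarifying sentence is still worth asking for.

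**Multiplicity belongs in an analysis plan, and this is a condensed article.** True of the adjustment method, whose absence alone would be no finding. Choosing the primary variable is different. Here the article makes that choice, and makes it inconsistently between the abstract, the outcome sections and the sizing paragraph.

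**Conclusion.** The primary outcome of the randomised phase is badly fixed. About 23 to 25 measures carry the primary label, including an alcohol screen and an exercise test without an outcome variable. The abstract names two domains. Only two comparisons are powered, one on an unidentified score, and no rule for success links them.

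The error rate is about 9 to 10% if either powered comparison may count (independence to correlation 0.5; 8.4% at 0.7). It is higher if any listed measure may count: 32 to 47% for 25 tests at assumed correlations of 0.7 to 0.5. Both figures assume an unadjusted two-sided 5% level. For measures other than the two powered ones, that level is inferred from its being the only one given. The point is worth correcting, but it does not show that the investigators intend 25 confirmatory tests or interim significance testing.

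**What to change.** Before any between-arm data are examined:

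1. Amend the abstract, both primary-outcome sections and Statistical Analysis so that they name the same two primary endpoints at 3 months: 400-m walk time, and the single quality-of-life score behind the 5-point calculation.
2. Test the two with Holm, or at 0.025 each, and state that rule as the criterion for success.
3. Move the other function tests and questionnaires to secondary or descriptive status.
4. Restate power at the adjusted level, giving the scale and SD for quality of life. At 0.025 a nominal 80% for the walk becomes about 71%, and quality of life falls from about 91% to 86% if its SD is 20 (assumed). Holm limits the loss, because once one endpoint succeeds the other is tested at 0.05.
5. As a clarification, add to Evaluation that the yearly evaluation during recruitment excludes the between-arm effectiveness comparison, which is made once, after the last 3-month assessment.

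No data collection changes. The cost is the power above and a substantive amendment to the protocol and the registration. The trial was registered in January 2019 and patients are already enrolled (265 in the abstract, 123 in the Results section), so the amendment should be dated and should state that it was made without sight of results by arm.
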